### Procedure

2.3

The participants will be initially informed about the objectives of the study in an introductory meeting involving also their family members. Following this meeting, the participants will provide their informed consent. No compensation or different treatment within the clinical institution practices will be reserved to participants included in the study. Participants will then undergo a neuropsychological battery exploring cognitive functions, affective symptoms and independence in daily living (T1). The same battery of tests will be repeated at the end of the first (T2) and of the second (T3) rehabilitation cycles. The intervention will involve two rehabilitation periods involving multifocal brain stimulation (real vs. sham with a crossover design) combined with cognitive stimulation therapy. EEG recordings with eyes-opened will be performed at the beginning and the end of each period of stimulation. The CONSORT Flow Diagram that will be ensued detailing enrolment, allocation, follow-up, and analyses is provided as Supplementary File.

### Intervention

2.4

The intervention will consist of multifocal brain stimulation combined with cognitive training. In a cross-over design, 16 stimulation sessions (two sessions for week; freely scheduled from Monday to Friday on participants’ and institutional needs) will be delivered in two blocks (8 real and 8 sham stimulation sessions) for 10 weeks. The first and the last stimulation sessions of each block (namely sessions 1, 8, 9 and 16; Figure 1) will be preceded and followed by 5-min resting state EEG recordings with eyes-opened. Recruited participants will be randomly assigned to a “SHAM-REAL” stimulation group (G1) or a “REAL-SHAM” stimulation group (G2; Figure 1) by computer-generated random numbers; one investigator (FP) will manage generation of allocation sequence and participants’ assignment to the groups. The experimenters responsible for delivering the stimulation (LC) will be blind to the stimulation being delivered during each session. Throughout the study, all participants will undergo traditional cognitive stimulation therapy, embracing within each session paper-and-pencil and computerized activities during a face-to-face interaction with the therapist at the rehabilitation service. Activities will target memory, attention, and executive functions (24, 25); the level of difficulty will be tailored on the patients’ neuropsychological profile and progressively adjusted based on patients’ response to the treatment. Each session of cognitive training will last 40 min and will follow the brain stimulation session.

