**Figure 2 fig2:**
[figure not shown]
Montage template and current distribution maps. **(A)** EEG and tDCS electrodes’ placement template; anodes placed over F3 and T7, return current distributed over the remaining electrodes; **(B)** current diffusion map of the left hemisphere; **(C)** current diffusion map of the right hemisphere.

The same electrodes used to deliver brain stimulation will serve for the EEG recordings derived before and after the stimulation sessions (sessions 1, 8, 9 and 16; Figure 1). The common mode sense (CMS) and the driven right leg (DLR) connections will be positioned on the right earlobe as electrical reference. Electrodes impedance for brain stimulation and recording will be checked before starting the session and monitored through its duration to ensure impedance values lower than 10 kΩ. Each EEG recording will last 5 min.

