### Sample size justification and statistics

2.8

The final sample size of 60 participants is estimated based on a sample size calculation on G*Power (v. 3.1.9.7) suggesting a sample size of at least 48 participants to compare the two groups along three-time points with an effect size = 0.25, power = 0.80, *ε* = 0.75, and a Bonferroni-adjusted *α* = 0.0125 (0.05/4 primary cognitive outcomes see below) and considering a dropout rate up to 30% from previous studies (37, 38).

Demographic data will be reported using descriptive statistics. Primary outcomes will be the measures of cognitive (MOCA, FAB, FCSRT, Stoop scores) and affective (GDS scores) functioning, while independence in daily living (ADL and IADL scores) and EEG parameters will be considered as secondary outcomes. Intention-To-Treat (ITT) analyses (39), which includes all randomized participants in the groups assigned, regardless of their adherence with the entry criteria, will be adopted. ITT analysis admits noncompliance and protocol deviations and gives an unbiased estimate of the intervention effect. Missing data will be dealt with by using a mixed-effect model approach which accommodates missing data under the missing-at-random assumption (40). To assess the effect of the intervention on multiple dependent variables simultaneously, repeated-measures analyses of variance (ANOVAs) will be conducted on the primary outcomes and secondary outcomes separately with the factors Group (G1 vs. G2) and Time (T1-T3). Moreover, multiple regression models will be used to identify the factors associated with the treatment outcome, considering gender, age, education, CRS scores, and EEG power spectrum at baseline as predictors and post intervention measures of general cognitive functioning (MOCA and FAB) and functional independence measures as criteria.

To assess possible sequence or carryover effects, an exploratory comparison of treatment effects between the two randomization arms (sham first over real vs. real first over sham) will be performed.

Statistical analysis will be performed using IBM® SPSS® Advanced Statistics and R package (R Foundation). Statistical significance will be set at *p* < 0.05.

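### The ANOVA fixed for EEG uses the three test visits (T1-T3), but EEG is recorded eight times on another schedule; no mapping is given and any mapping drops the post-washout baseline and the full set of pre/post-session changes

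*Protocol article*

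**What the plan says.** Section 2.8 (Sample size justification and statistics) classifies the outcomes: "independence in daily living (ADL and IADL scores) and EEG parameters will be considered as secondary outcomes". In the same paragraph, the repeated-measures ANOVAs "will be conducted on the primary outcomes and secondary outcomes separately with the factors Group (G1 vs. G2) and Time (T1-T3". EEG is not exempted.

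The three time points are defined by the test battery. Section 2.3 (Procedure) introduces the first: "Participants will then undergo a neuropsychological battery exploring cognitive functions, affective symptoms and independence in daily living (T1". It then places T2 at the end of the first rehabilitation cycle and T3 at the end of the second. Section 2.5 and the Figure 1 caption use T1-T3 in the same sense.

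EEG timing is described separately:

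- Section 2.3: "EEG recordings with eyes-opened will be performed at the beginning and the end of each period of stimulation".
- Section 2.4 (Intervention): "The first and the last stimulation sessions of each block (namely sessions 1, 8, 9 and 16; Figure 1", and these sessions "will be preceded and followed by 5-min resting state EEG recordings with eyes-opened".
- Text after Figure 2, on the montage: "EEG recordings derived before and after the stimulation sessions (sessions 1, 8, 9 and 16; Figure 1".

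Section 2.7 computes power in four frequency bands for each participant and session, without saying whether the recording before or after the session is meant.

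**The concern.** An article may leave modelling detail to a full analysis plan. Here, however, it names the time factor and its levels for the secondary outcomes, and those levels do not fit how EEG is collected. Whoever follows the text must first decide which recordings represent T1, T2 and T3, and nothing in the document settles that before the data are seen.

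The choice affects what the result means. The schedule carries two kinds of information: the change from before to after a session, and the change from the first to the last session of a block. It also gives a fresh baseline at the start of the second block, after the one-week washout. The test battery is not repeated at that point, so the recording before session 9 is the only outcome measurement scheduled there. A three-level Time factor has no place for it and no pre/post factor. EEG is collected to show the neurophysiological effect of the intervention and to look for markers of response, so recordings made for that purpose would be set aside.

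**Working it through.** **1. The plan's own figure.** Section 2.8 gives at least 48 participants for two groups and three time points, with f = 0.25, power 0.80, epsilon 0.75 and alpha 0.0125. No correlation between repeated measures is stated; I assume 0.5. For the within-between interaction:

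- lambda = f² x N x m x epsilon / (1 - rho) = 0.0625 x 48 x 3 x 0.75 / 0.5 = 13.5
- df1 = (2 - 1)(3 - 1) x 0.75 = 1.5
- df2 = (48 - 2)(3 - 1) x 0.75 = 69
- power = 0.816, and 48 is the smallest even N that reaches 0.80.

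The figure reproduces and describes outcomes measured at T1-T3. For illustration only, eight measurements under the same assumptions would need N = 26, so the mismatch is not a sample-size shortfall.

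**2. Counting recordings.** 4 sessions (1, 8, 9, 16) x 2 recordings (before, after) = 8 per participant, against 3 levels of Time.

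**3. Plausible mappings.** T1 precedes treatment, so only the recording before session 1 fits. T2 is the end of cycle 1: before or after session 8. T3 is the end of cycle 2: before or after session 16. That gives 1 x 2 x 2 = 4 mappings, or 2 if the same side of the session is used at T2 and T3. Each uses 3 recordings and leaves 8 - 3 = 5 unused, always including both recordings at session 9.

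**4. What each mapping measures in block 1.** If T2 is taken before session 8, the T1-T2 change is pre8 - pre1, a change over the block. If T2 is taken after session 8:

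post8 - pre1 = (pre8 - pre1) + (post8 - pre8)

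This adds the within-session change to the block change, and a three-level Time factor cannot separate the two parts.

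**5. What happens in block 2.** With recordings taken before the session:

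T3 - T2 = pre16 - pre8 = (pre16 - pre9) + (pre9 - pre8)

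The second term is the change over the washout. Suppose real stimulation adds d over a block relative to sham, a fraction r of d is lost in the washout, and there is no further loss in block 2. Changes common to both groups cancel.

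| Comparison of groups | Expected difference |
|---|---|
| T1 to T2, real-first minus sham-first | d |
| T2 to T3, sham-first minus real-first | d + r x d = (1 + r)d |
| Pre-session 9 to pre-session 16, sham-first minus real-first | d |
| Pre-session 1 to pre-session 9, real-first minus sham-first (carryover check) | (1 - r)d |

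Group x Time therefore does contain the real-sham contrast, but in block 2 it is mixed with the washout loss: between d (r = 0) and 2d (r = 1). The recording before session 9 separates the two.

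**6. Multiplicity, as a range.** Section 2.8 sets significance at p < 0.05. The article does not say how electrodes are combined. If no effect exists, four band averages give 4 x 0.05 = 0.2 expected false positives per effect tested. Four bands at each of the 8 electrodes give 32 x 0.05 = 1.6. The range is 0.2 to 1.6, depending entirely on that assumption.

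**The case against.** The strongest reply is that EEG brackets the test visits: there is a recording before session 1, and there are recordings at the last session of each block. A Group x Time (T1-T3) analysis of EEG can therefore be run. The article never states an aim of separating within-session from cumulative effects. The planned search for predictors of outcome uses baseline EEG power in a regression that does not depend on this ANOVA. Which recording enters a secondary model is the kind of detail a full plan could settle.

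Much of this stands, and it rules out several stronger readings that a reader might infer:

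- *That no EEG data correspond to T1-T3.* Not supported; a subset aligns.
- *That any three of the eight recordings could be chosen* (8 x 7 x 6 / 6 = 56 ways). Not supported; the definitions of T1-T3 leave 2 to 4.
- *That real and sham are not compared.* Not supported; the contrast sits inside Group x Time.
- *That the EEG aims cannot be met.* Not supported; the baseline regression is unaffected, and the recordings themselves would support a fuller model.
- *That about 1.6 false positives per effect should be expected.* This is only the upper end, and it assumes testing electrode by electrode.

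The appeal to an unseen full plan does not stand. The article is not silent: it fixes three levels that do not match the EEG schedule, and following it literally drops the post-washout baseline and the pre/post factor. The limit lies in the stated model, not in the design.

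**Conclusion.** The point holds as a mismatch between a stated analysis and the data it is applied to. Eight recordings per participant meet a three-level Time factor with no mapping. Any of the 2 to 4 plausible mappings leaves 5 of 8 recordings unused, omits the post-washout baseline and cannot separate within-session from block change. The real-sham contrast is carried only indirectly and, in block 2, is mixed with whatever happens in the washout.

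The conclusion rests on reading section 2.8 as written, with EEG among the secondary outcomes analysed over T1-T3. The d to 2d range also needs the simple carryover assumptions stated with it. The matter should be corrected before data are examined, but it concerns a secondary outcome. It does not affect the sample size, the test-battery outcomes or the baseline-EEG regression.

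**What to change.** State in section 2.8 that EEG is exempt from the T1-T3 ANOVA. Analyse all eight recordings in a mixed model on transformed band power, with treatment (real or sham), session in block (first or last), pre/post, period, sequence and a random participant effect, plus the interactions that the named contrasts need.

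Before data are examined, name these real-versus-sham contrasts:

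- change over a block: pre-session 8 minus pre-session 1, and pre-session 16 minus pre-session 9;
- change within a session: post minus pre.

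Use the recording before session 9, compared between groups relative to pre-session 1, as an exploratory carryover check. Say how electrodes are combined, and label all other EEG tests exploratory.

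A single sentence mapping recordings to T1-T3 would remove the ambiguity but would still discard the session-9 baseline and the within-session change.

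Cost: analysis wording and slightly more modelling work. No new recordings or visits are needed.

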### Neuropsychological assessment

2.5

A brief battery of neuropsychological tests will be used to monitor cognitive functions, affective symptoms and independence in the participants involved in the treatment (T1, T2, T3; Figure 1).

*Montreal Cognitive Assessment* [MOCA; (26)]. MOCA is a brief neuropsychological tool for screening global cognitive functioning specifically designed for MCI and early stages of dementia. The test includes 8 sub-tests assessing: executive functions, visuo-spatial abilities, naming, short-term and long-term episodic memory, attention, lexical access, abstraction, spatial and temporal orientation. The test provides a maximum score of 30; the higher the score, the higher the level of global cognitive efficiency.

*Frontal Assessment Battery* [FAB; (27)]. FAB is a screening neuropsychological battery including 6 sub-tests for evaluation of executive functioning: classification, mental flexibility, motor programming, sensibility to interference, inhibitory control and environmental autonomy. The total score is up to 18; the higher the score, the higher the level of executive functioning.

*Free and Cued Selective Reminding Test* [FCSRT; (28)]. FCSRT is designed to assess episodic memory domain. The test entails learning 12 pictorial stimuli (6 living and 6 non-living), followed by free and cued recall tasks. It assesses immediate and delayed recall, both free and cued, as well as recognition ability. The FCSRT is sensitive to memory impairments where recall does not significantly improve with cues, rendering it a valuable tool for identifying early signs of the disease. The test provides separate scores for free, cued and total *immediate* recall (maximum score 36), and scores for free, cued and total *delayed* recall (maximum score 12). For these measures the higher the scores, the higher the memory performance. Moreover, the FCRS provides a cue-sensitivity index (range 0–1) representing the extent of facilitation using the semantic cues in memory recall.

*Stroop Color and Word Test* (29). The Stroop Test aims at assessing the ability to inhibit cognitive interference. Participants are presented with three tables and are required to respond as quickly as possible. Two tables represent the ‘congruent condition’: in the former participants have to read color names (hereafter referred to as color words) printed in black ink, and in the latter, they are required to name color patches. Conversely, in the third table, the so-called color-word condition, the color words are printed in an incongruent color (for example, the word ‘red’ is printed in green ink), and participants have to name the color of the ink instead of reading the word. The test provides two measures, i.e., overall number of errors and time to complete the test, with higher scores indicating worse performance.

*Geriatric Depression Scale* [GDS; (30)]. GDS is a specific evaluation tool to diagnose severity of depression symptoms in older adults. This questionnaire, including 30 items, is designed for the older person and defines his/her degree of satisfaction, quality of life, and feelings. The maximum score is 30 with higher scores indicating higher levels of depression.

*Cognitive Reserve Scale* [(31); CRS; (32)]. The Italian version of the CRS is a self-rated questionnaire evaluating the engagement of a person in several activities, i.e., daily activities, training or information, hobbies, and social life. The CRS allows to assess CR in three life stages: young adulthood (18–35 years), middle adulthood (36–64 years), and late adulthood (≥65 years). According to their ages, participants have to complete the questionnaire once, twice or three times referring to the main activities during young adulthood, middle adulthood and late adulthood. Each of the 24 items is scored on a Likert scale based on the frequency each activity is performed during a week (0 = never; 4 = twice or three-time a week). The total score of the CRS is obtained by the sum of each item (maximum score 96). The higher the score, the higher the level of CR. Depending on the age of participants the scores is averaged for each of the age period.

*Independence in Everyday Life*. To monitor functional independence two scales will be adopted. The Activities of Daily Living [ADL; (33)] scale targets activities concerning care of one’s own body, such as bathing, toileting, dressing and eating; it includes six items with a maximum score of 6. The Instrumental Activities of Daily Living [IADL; (33)] scale refers to activities to support daily life within the home and community, such as financial management, housekeeping, shopping for groceries, making telephone calls, and taking medication; it includes eight items with a maximum score of 8. Both scales will be administered to patients’ caregivers. For both scales, the higher the score the higher the level of functional independence.

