### Participants

2.2

The recruitment centers for the study will be “Alma Mater Camaldoli Hospital” (Naples) and the Neuropsychological Testing Service of the Department of Psychology of University of Campania “Luigi Vanvitelli” (Caserta) in Italy. All participants consecutively admitted to the two centers will be screened for study participation. Data collection will be terminated when at least 60 participants will complete the whole intervention. Inclusion criteria are: (i) age between 55 and 85 years, and (ii) diagnosis of minor neurocognitive disorder, or major neurocognitive disorder with mild severity, according to Diagnostic and Statistical Manual of Mental Disorders [DSM-5; (20)] with a Clinical Dementia Rating Scale (CDR) of 0.05 or 1 (21), (iii) right handedness. The diagnosis will be made by expert neurologists and neuropsychologists. Exclusion criteria are: (i) brain events with an acute aetiology (stroke, traumatic brain injury, neoplastic ablation), (ii) psychiatric disorders (schizophrenia, psychosis, bipolar disorder) and assumption of psychotropic drugs, (iii) diagnosis of moderate or severe major neurocognitive disorders [DSM-5; (20)] with CDR scores equal or above 2 (21), (iv) any condition which might even hypothetically interfere with electrophysiological recording and neurostimulation (metallic implants in the brain, cochlear implant, pacemakers, epilepsy) (22, 23).

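### The Cognitive Reserve Scale predictor takes in current activity for participants aged 65 and over, and no baseline cognition or severity term is listed, so its regression coefficient can be inflated if activity falls with severity

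*Protocol article*

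**What the plan says.** All of this is in the protocol article.

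- **Eligibility (2.2 Participants).** Entry requires "age between 55 and 85 years" and a "diagnosis of minor neurocognitive disorder, or major neurocognitive disorder with mild severity".
- **CRS stages (2.5 Neuropsychological assessment).** The self-rated questionnaire asks how often activities are done in "young adulthood (18–35 years), middle adulthood (36–64 years), and late adulthood (≥65 years"). It adds: "According to their ages, participants have to complete the questionnaire once, twice or three times".
- **CRS scoring (2.5).** Each of 24 items is scored 0 to 4 and summed. Then: "Depending on the age of participants the scores is averaged for each of the age period".
- **Use (2.8 Sample size justification and statistics).** The multiple regressions are specified as "considering gender, age, education, CRS scores, and EEG power spectrum at baseline as predictors", with "post intervention measures of general cognitive functioning (MOCA and FAB) and functional independence measures as criteria".

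The predictors in 2.8 do not include baseline MOCA or FAB, or the Clinical Dementia Rating. The Abstract gives the purpose of these regressions as finding how far education and cognitive reserve may influence the results of the intervention.

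**The concern.** The eligible age range straddles the 65-year boundary of the scale. Everyone in the trial has lived through the first two stages, and only those aged 65 or over have a third. For them the third stage is the one they are living in with MCI or mild dementia. The scale counts how often activities are done, and impairment can plausibly reduce that.

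Severity could then lower both the late-stage CRS score and the post-intervention MOCA, FAB and functional scores. With no baseline or severity term in the model, part of that association would be credited to reserve. The article wants to use such factors to identify suitable patients, so an inflated CRS coefficient would mislead on a stated aim, although not on the treatment comparison.

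**Working it through.** **The plan's own figure.** 24 items x 4 points = 96, the stated CRS maximum. It reproduces.

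**Composition of the score, pooled reading.**
- Age 55-64: (young + middle) / 2.
- Age 65-85: (young + middle + late) / 3, so the late stage carries one third of the weight even for someone who has just turned 65.

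Illustration with the same earlier life:
- Age 64, stages 50 and 50: score 50.0.
- Age 65, stages 50, 50 and 30: (50 + 50 + 30) / 3 = 43.3.

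The 20-point fall is only illustrative. Mean late-stage falls of 5, 10 or 15 points shift the score by 5/3 = 1.7, 10/3 = 3.3 or 15/3 = 5.0 points.

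**Does this bias the slope?** The article gives no CRS variances, correlations or link with severity, so every input below is an assumption.

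*Large-sample simulation (n = 400,000).* Ages are uniform from 55 to 85. Reserve R and severity S are independent with SD 1. Each stage equals R plus error of SD 0.5. The late stage is lowered by 0.5 SD on average and by g SD per SD of severity. The outcome is 0.30R - 0.5S - 0.02(age - 70) plus noise of SD 0.7. The outcome is regressed on age and CRS.

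| g | Two-stage mean | Score as written | As written, severity also in model |
|---|---|---|---|
| 0 | 0.266 | 0.272 | 0.272 |
| 0.25 | 0.266 | 0.296 | 0.272 |
| 0.5 | 0.266 | 0.318 | 0.272 |
| 1.0 | 0.267 | 0.350 | 0.267 |

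- The two-stage slope is below 0.30 because of measurement error: 0.30 / (1 + 0.25/2) = 0.267.
- With g = 0 the two scores agree within 2% (0.272/0.266), despite the uniform late-life fall. That gap is only the better reliability of three stages.
- With a severity link the ratios are 0.296/0.266 = 1.11, 0.318/0.266 = 1.20 and 0.350/0.267 = 1.31. Against the g = 0 value of the same score they are 1.09, 1.17 and 1.29.
- At g = 0.25 the slope (0.296) is still just under the assumed true 0.30. At 0.5 and 1.0 it exceeds it.
- With severity in the model the inflation disappears.

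*If the middle stage of those aged 55-64 is also contaminated* (by 30% of the same reduction), at g = 1.0 the two-stage mean gives 0.288 and the score as written 0.371. Against 0.266 that is +8% and +39%.

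*Null simulation (n = 60, 4,000 trials per scenario, no effect of reserve).* Stage SD is 12 points, between-stage correlation 0.65, outcome-severity correlation 0.5 to 0.7. Late-stage activity falls by 3, 6 or 9 points per SD of severity.
- Score as written: the CRS term is significant at 0.05 in about 6%, 7-11% or 10-17% of trials (overall 5.5% to 16.8%).
- Two-stage mean: 4.4% to 5.7%. The simulation error around 5% is sqrt(0.05 x 0.95 / 4000) = 0.34 percentage points, so this range, and the 5.5% above, cannot be told from the nominal rate.

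A further null simulation (outcome-severity correlation 0.6), which allowed contamination of the middle stage, gave a spurious slope of 0.04 to 0.20 outcome SD per 12 CRS points as written. The two-stage mean gave 0.00 to 0.09.

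**The case against.** **The scoring sentence is ambiguous.** It can mean one pooled average or a separate score per stage, and 2.8 uses the plural for the CRS. With stage-specific scores the definition does not change at 65. This stands as a limit. However, nobody aged 55-64 can have a late-adulthood score, so a complete-case regression on it would drop them. Either reading needs a clarifying sentence.

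**The cause is the missing severity term rather than the averaging.** This is largely right: inflation appeared only when late activity tracked severity and severity was left out. That is why the fix includes the baseline outcome.

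**The two-stage mean is not clean either.** For participants aged 55-64 the middle stage includes recent, possibly symptomatic years. This stands too: the bias is reduced, not removed.

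**The scale explicitly covers late adulthood, and current activity is a legitimate predictor of who responds.** For pure prediction that is fair. It is less fair for the Abstract's question of how far reserve influences outcome.

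**Stronger readings that the article does not support.**
- *That the regression is shown to be biased.* The article has no data on the link between activity and severity.
- *That the switch from two to three stages at 65 is itself the harm.* With age in the model, it left the slope essentially unchanged.
- *That the CRS nearly duplicates ADL and IADL.* The CRS items are not listed, at most one of its four areas (daily activities) overlaps, and it is self-rated, whereas ADL and IADL are given to caregivers.

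**Conclusion.** The point holds in conditional form. On the natural reading of 2.5, the CRS score of participants aged 65 or over includes current activity under MCI or mild dementia, and 2.8 lists nothing that would separate reserve from severity. If current activity falls with severity by 0.25 to 1.0 SD per SD, the coefficient is inflated by about 11% to 31% relative to the two-stage score. Under a null effect, falls of 3 to 9 points per SD of severity put the false-positive rate at about 6% to 17%. At the low end the effect is negligible. These sizes rest entirely on assumed inputs.

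A reader might infer that the efficacy results are at risk. They are not: the CRS enters only the supporting regressions, so the Group by Time comparison and the sample size do not depend on it. This is a cheap improvement to a supporting analysis.

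**What to change.** In sections 2.5 and 2.8:

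1. State that the CRS predictor is the mean of the young- and middle-adulthood scores for every participant. All eligible participants complete both.
2. Report the all-stages average alongside as a sensitivity analysis.
3. Keep the late-adulthood score as a descriptive variable of current activity.
4. Add the baseline (T1) value of the outcome to each regression. As an imperfect proxy for severity it narrows this channel, but need not close it as fully as the severity term did in the simulation.

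**Cost.** A sentence or two of text, and one more regression parameter per model. No new data, visits or patients are needed, because the questionnaire is completed stage by stage and the T1 battery is already planned. The downsides are that the main predictor departs from the all-stages score, rests on two stages instead of three for those aged 65 or over, and still includes recent years for those aged 55-64.
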